## Abstract

**Background:**

Airway clearance techniques (ACTs) for individuals with bronchiectasis are routinely prescribed in clinical practice and recommended by international guidelines, especially during an acute exacerbation. However, there is limited evidence of the efficacy of these techniques during an exacerbation to improve sputum expectoration, health-related quality-of-life (HRQOL) or exercise tolerance. The primary aim of this study is to compare the effects of the active cycle of breathing technique (ACBT), oscillating positive expiratory pressure (O-PEP) therapy, and walking with huffing on sputum expectoration for adults hospitalised with an acute exacerbation of bronchiectasis. Secondary aims are to compare the effects of these interventions on HRQOL, health status, exacerbation rates and hospital admissions in a six-month period following hospital discharge.

**Methods:**

This multi-centre randomised controlled trial will recruit adults with an acute exacerbation of bronchiectasis requiring hospital admission. Participants will be randomised to receive one of three interventions: ACBT, O-PEP therapy, and walking with huffing. Outcome measures including sputum volume during and 1-h post ACT session, and 24-h sputum, as well as health status, HRQOL and exercise capacity will be completed during inpatient stay on day 2 and day 6 of admission, and within 24 h of hospital discharge. Time to first exacerbation, and time to first hospitalisation will be monitored via monthly phone calls for six months post hospital discharge. Health status and HRQOL will be assessed after discharge at two and six months, and exercise capacity will be assessed at six months post hospital discharge.

**Discussion:**

Despite recommendations regarding the importance of ACT for individuals with bronchiectasis during an acute exacerbation, there is a gap in the literature regarding effectiveness of ACT when undertaken by individuals in this clinical state. This study will add to the evidence base regarding the effectiveness of commonly implemented ACTs during a hospital admission with an exacerbation of bronchiectasis. Additionally, it will contribute to knowledge of the long term effects on important and patient-centred outcomes, including incidence of future exacerbations, and HRQOL, which has not been previously established.

*Trial registration* Registered on the Australian and New Zealand Clinical Trials Registry (ACTRN12621000428864).

## Introduction

Bronchiectasis is a chronic and progressive respiratory condition which is characterised by chronic cough, sputum production, shortness of breath, recurrent exacerbations, and decreased exercise tolerance [1–3]. Recurrent exacerbations have been shown to lead to progressive deterioration of lung function [4] and poorer health-related quality of life (HRQOL) [5], and account for a higher mortality rate [6]. An exacerbation is defined as a deterioration in three or more of the following symptoms for at least forty-eight hours: cough; sputum volume and/or consistency; sputum purulence; haemoptysis, breathlessness and/or exercise tolerance; fatigue and/or malaise [7].

Airway clearance techniques (ACTs) are routinely used as part of a physiotherapy treatment regimen for people with bronchiectasis, with most individuals experiencing excessive secretions due to increased sputum production and difficulty in clearing these secretions secondary to airway damage [2, 8–10]. The goals of ACTs are to provide more effective sputum clearance to improve ventilation, as well as reduce cough and breathlessness impact, therefore improving HRQOL [11]. International guidelines recommend ACTs are taught routinely to people with bronchiectasis, and state that during an acute exacerbation of bronchiectasis, an individual should be reviewed daily and that a change in ACT may be required [12–14]. Previous research on ACTs has been completed on individuals who are clinically stable [15–17], but there is little evidence available regarding the effectiveness of ACTs during an acute exacerbation [10, 15]. Furthermore, due to differences in sputum volume and consistency, extrapolating evidence from those in a stable clinical state may be misleading in estimating the effect for individuals during an acute exacerbation [18].

Two of the most commonly implemented ACTs internationally are the active cycle of breathing technique (ACBT) and oscillating positive expiratory pressure (O-PEP) therapy [8, 19–23]. In a recent survey of physiotherapists working in Australia and New Zealand, both the ACBT and O-PEP therapy were found to be frequently used [23]. The ACBT was used very often or always by 89% of participants managing adults with an acute exacerbation of bronchiectasis [23]. It was perceived to be effective in this patient population by 90% of physiotherapist participants in the same study. The same survey reported that O-PEP therapy was used routinely by 75% of participants and was perceived to be very effective or effective by 97% of clinician participants managing adult patients during an acute exacerbation of bronchiectasis [23]. In a recent study investigating ACT use in individuals with bronchiectasis in the United States by analysing data from the United States Bronchiectasis Registry, the most commonly used ACT was O-PEP devices (44%) followed by multiple modalities (43%) [21]. A study exploring ACT use based on findings from the European Bronchiectasis Registry (EMBARC) found the most commonly implemented ACT was the ACBT (26.8%) [22].

The ACBT is an ACT which uses modulation of breathing to employ the physiological effects of interdependence and collateral ventilation to improve ventilation, which when combined with a huff will aid secretion clearance [11]. The ACBT has been used for many years in a range of respiratory conditions [24], requires no equipment and can be completed in differing positions [11, 25].

Oscillating PEP therapy involves a device designed to provide positive expiratory pressure and endobronchial pressure oscillation to loosen secretions from the airway walls [26, 27]. There are a range of devices available including Aerobika®, Flutter Valve®, Acapella® and Lung Flute® [21]. All devices are designed to utilise collateral ventilation to improve ventilation distribution, and direct airflow behind secretions, as well as splint open the airways using positive expiratory pressure [28]. The oscillation of endobronchial pressure is designed to alter the viscosity of secretions to allow their movement towards the larger airways in preparation for expectoration [28].

The goal of ACBT and O-PEP therapy is to facilitate secretion removal, therefore an improvement in sputum removal would correspond with an increase in sputum expectorated during or immediately following an airway clearance session, plus or minus a decrease in sputum expectoration in the 24 h following an airway clearance session [17, 29, 30]. A recent international guideline also recommended implementation of the ACBT or O-PEP therapy for individuals with stable bronchiectasis (level D—low level evidence), based on current evidence available [12]. In individuals with a range of chronic respiratory diseases, the ACBT has been shown to be beneficial in the short term for improving sputum wet weight, forced expiratory volume in 1 s (FEV_1_) and forced vital capacity (FVC), when compared to other types of ACTs [24, 31]. Oscillating PEP therapy has been shown to be equal to other ACTs in improving sputum expectoration and lung function [15], and demonstrated improvements in both sputum expectoration and HRQOL in individuals with stable bronchiectasis compared to no treatment [16, 28]. It has also been shown to be a preferred ACT by individuals with bronchiectasis compared to other ACT options, which may improve compliance with therapy [10].

Although both the ACBT and O-PEP therapy have demonstrated benefits in patients who are clinically stable, [25, 28, 32, 33], there is limited evidence for these techniques in individuals experiencing an acute exacerbation of bronchiectasis. One systematic review investigated ACTs during an acute exacerbation and highlighted the limited evidence available, with only six studies published, and encompassing 120 participants [10]. The key findings were all implemented ACTs appeared safe during an acute exacerbation and the ACBT was found to be superior in sputum expectoration (greater decrease in 24 h collection), cough-related quality of life and gas exchange when compared to more traditional ACTs of percussion and postural drainage [10]. Oscillating PEP therapy was preferred by participants over other types of ACTs [10]. However, the long-term effects of these treatments on clinically important and patient-centred outcomes, including incidence of future exacerbations, HRQOL and health status have not been established [10].

Exercise or physical activity is routinely used as part of physiotherapy management of individuals with bronchiectasis, including during an acute exacerbation [19, 34] and has recently been reported as a potential substitute for traditional ACTs in patients with chronic respiratory diseases [35]. Traditionally, walking is the most commonly clinically implemented exercise during an acute exacerbation, and the goal is to maintain function, minimise the effect of bed rest and facilitate hygiene care and activities of daily living [36]. The potential for it to also be a standalone ACT is based on the physiological rationale that exercise, particularly walking, may increase expiratory airflow, decrease sputum mechanical impedance, improve ease of expectoration, increase volume of secretions cleared and increase cough [37, 38]. Although exercise as a standalone ACT has not been investigated in bronchiectasis, there is emerging evidence for this option in cystic fibrosis (CF) and chronic obstructive pulmonary disease (COPD) [38, 39]. Exercise as an ACT in the cystic fibrosis population has been shown to improve ease of expectoration and sputum clearance when compared to rest, and may have similar short-term effects for airway clearance as traditional ACTs [35, 36]. Exercise has also been explored in individuals with COPD, with one study investigating the effect of usual care including an exercise program compared to PEP therapy during an acute exacerbation of COPD [39]. The exercise program consisted of implementing a walking program (or equivalent lower limb exercise), with the aim of achieving 30 min/day combined with coughing. No significant differences were found between groups on symptoms, quality of life and future exacerbations, suggesting usual care incorporating exercise and coughing is just as effective as PEP therapy in achieving key outcomes following acute exacerbations of COPD [39]. Although, traditionally, evidence for ACT and other therapies for bronchiectasis has been extrapolated from other respiratory populations, there are some key differences between these conditions which highlight the importance of research for bronchiectasis. Of particular relevance are the differences in sputum rheology and electrolyte content [40]. The differences in sputum characteristics may lead to ACTs demonstrating differing results in clinically important outcome measures.

### Research aims

The primary aim of this randomised controlled trial is to compare the effects of the ACBT, O-PEP therapy and walking with huffing (control condition) on sputum expectoration for adults hospitalised with an acute exacerbation of bronchiectasis. Secondary aims are to compare the effects of these three interventions on HRQOL, health status, exacerbation rates and hospital admissions in a six-month period following this hospital admission.

## Methods

### Design

This study will be a 6-month prospective, parallel-groups, randomized, controlled trial comparing the short and long-term effects of ACBT, O-PEP therapy, and walking with FET, in adults hospitalised with an acute exacerbation of bronchiectasis. The full study protocol was registered with the Australian and New Zealand Clinical Trials Registry (ACTRN12621000428864). Ethics approval was received from the Uniting Care Human Research Ethics Committee (Reference number 2020), Bond University Human Research Ethics Committee (Reference number UCH HREC2020), Charles Sturt University Human Research Ethics Committee (Protocol number H21027) and Monash University Human Research Ethics Committee (Project number 27817).

### Participants

Participants will be adults (age 18 years and over) admitted to one of two collaborating private hospitals in Brisbane, Australia, with an acute exacerbation of bronchiectasis, defined by internationally accepted criteria [7]. Exclusion criteria include: primary diagnosis of a respiratory condition other than bronchiectasis, breathing through an artificial airway or requiring non-invasive ventilation within 48 h of hospital admission, or any contraindication to ACBT or O-PEP therapy, including undrained or drained pneumothorax within the last 6 months, post lung lobectomy or lung transplant, haemodynamic instability or severe cardiovascular disease, undrained empyema or lung abscess, active haemoptysis, middle ear infection, previous recruitment and completion/withdrawal from this study, or hyper-reactive airways as diagnosed by a respiratory physician during the hospital admission [41–43]. Potential participants requiring high flow oxygen therapy will still be eligible to participate. A recent hospital admission/exacerbation will not exclude potential participants from being included in the study.

Participants will be assessed for potential inclusion in the first 48 h of hospital admission; if they meet any of the exclusion criteria at this time, they will be deemed ineligible and not reassessed for inclusion later in their hospital admission.

### Recruitment and randomisation

The flow of participants through the study is available in Fig. 1. The participant timeline is available in Fig. 2. Potential participants will be identified via two means; firstly, the research assistant checking for new hospital admissions daily, secondly; new admissions will be flagged to the research team from nursing, medical, and physiotherapy staff who identify potential participants. Screening for potential participants will occur seven days per week during the participant recruitment phase. Additionally, training sessions for physiotherapy staff at both hospitals will be run by the chief investigator throughout the recruitment period to ensure all staff are aware of the study and inclusion criteria. Once identified, potential participants will initially be approached by the chief investigator or a research assistant to provide verbal and written information on the study protocol. If the potential participant provides written consent to participate in the study, then baseline outcome measures will be collected prior to group allocation.

**Fig. 1 Fig1:**
[figure not shown]
Participant flow diagram. *ACBT* active cycle of breathing technique, *FET* forced expiration technique, *O-PEP* oscillating positive expiratory pressure

**Fig. 2 Fig2:**
[figure not shown]
Participant timeline. *ACBT* Active cycle of breathing technique, *BEST* Bronchiectasis Exacerbations and Symptoms Tool, *DC* Discharge, *g* Grams, *O-PEP* Oscillating positive expiratory pressure therapy, *Q* Questionnaire, *6MWT* Six-minute walk test

Baseline assessment of the severity of bronchiectasis will be completed on enrolment to the study, and prior to random allocation to intervention groups, and scored according to the Bronchiectasis Severity Index, a validated measure of disease severity [6]. During the hospital admission, growth of bacterial organisms (such as Pseudomonas Aeruginosa, Haemophilus Influenzae) in sputum samples will be recorded [14] for further characterisation of specific presentations of participants.

### Allocation

Participants will be randomly assigned to one of three groups, based on a computer-generated random sequence, with the allocation stratified by participant self-reported usual volume of sputum production (low volume (< 1 teaspoon sputum per day when well) or high volume (> 1 teaspoon sputum per day when well) [44]) to ensure a balance between groups in this characteristic. The computer-generated random allocations will be placed into numbered sequences (one for each strata) of opaque envelopes by the chief investigator, which will only be opened by the treating physiotherapist once baseline measures are completed. Only participants and treating physiotherapists will have knowledge of the group allocation. Blinding of assessors to treatment allocation will be achieved through the assessor not accessing medical documentation for the participant, participants being requested to place any handouts or equipment out of sight (e.g. in a drawer) prior to the assessor entering the room, and the participants being asked not to discuss any intervention with the assessor. The assessors will report any instances of unblinding and these will be recorded. The assessors will be senior cardiorespiratory physiotherapists who are not involved in the patient’s care during the admission.

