#### Statistical methods

Data analysis will be performed using SPSS V.28 (SPSS, Chicago, Illinois, USA). Data will be analysed using intention-to-treat principles, with alpha set at 0.05 for inferential analyses.

Data will be described as mean (standard deviation) or median (interquartile range) for continuous outcomes depending on distribution, and as frequency (percentage) for categorical outcomes. Demographic data, including age, pseudomonas aeruginosa colonisation, bronchiectasis severity scores and QoL-B scores will be compared to findings from the Australian Bronchiectasis Registry to determine external validity of the study findings. Where participants have a comorbid respiratory condition (such as Asthma or COPD), this will be noted and reported in the data analysis, and considered during interpretation of the findings of the study and when discussing the generalisability of findings.

The primary outcome, between-group difference in sputum volume over a 24-h period will be assessed using mixed-effects linear regression models, with treatment group and time included as main effects, and a group-by-time interaction term. Participant will be included as a random effect to account for the repeated measures nature of the data.

Secondary outcome measures with continuous outcomes will be analysed using linear regression, with binary outcomes using logistic regression, and with count outcomes using Poisson regression models. Repeated measures models will be used when appropriate. When data does not fit regression assumptions, non-parametric methods such as the Kruskal–Wallis test will be used to compare differences in scores on each instrument between groups at each of the different time points. Time-to-event outcomes, such as time to first recurrence of an exacerbation following discharge from initial hospital admission, will be visualised using Kaplan Meier survival curves and analysed using Cox proportional hazards regression.

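### The primary mixed model leaves out the sputum-volume stratum used in randomisation, giving up some precision in the between-group contrasts

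*Protocol article*

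**What the plan says.** Under Allocation, participants are randomised to three groups "with the allocation stratified by participant self-reported usual volume of sputum production", with the stated aim "to ensure a balance between groups in this characteristic". There are two strata, below and above one teaspoon a day when well, each with its own envelope sequence. The section does not say whether the sequences are blocked.

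Under Statistical methods, the between-group difference in 24-hour sputum is assessed with "mixed-effects linear regression models, with treatment group and time included as main effects, and a group-by-time interaction term". The next sentence adds: "Participant will be included as a random effect to account for the repeated measures nature of the data". No other term is named.

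For the secondary outcomes the section names model families only. For example, "Secondary outcome measures with continuous outcomes will be analysed using linear regression". No terms are listed for any of these models, not even treatment group.

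**The concern.** Usual sputum volume is the only stratification factor, and it is closely related to the primary outcome. If it is prognostic, the analysis should use it. A stratum that varies between participants but is left out of the model moves into the participant random effect and widens the interval for a group difference at any one time. If the randomisation also forces balance on it, the unadjusted standard error overstates the real sampling error and the test becomes conservative.

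This is more than silence that an unseen analysis plan might fill, because the primary model's terms are written out and the stratum is missing from the list. Precision matters here: the design rests on 17 analysed participants per group, and Sample size concedes that the recruitment target may not be reached.

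**Working it through.** **Inputs from the protocol (Sample size):** difference δ = 15 ml, SD σ = 15 ml, α = 0.05 (taken as two-sided; the protocol does not say), 17 per group.

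**Input that is assumed:** R², the share of variance in 24-hour sputum explained by the stratum. The protocol gives no value, so a range is shown.

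**1. Reproduce the planned figure.** In a two-sample t-test with δ/σ = 1, 80% power needs n = 16.7, so 17 per group, with power 0.807. The stated sample size is therefore an unadjusted calculation and does not rely on the stratum.

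**2. Add the stratum.** The residual SD is 15·√(1 − R²). The standard error of a two-group contrast is that SD times √(2/17) = 0.343. The noncentrality is 15 divided by the standard error, with 2·17 − 3 = 31 degrees of freedom.

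| R² | Residual SD (ml) | SE (ml) | Noncentrality | Power at 17 per group | Interval width, unadjusted ÷ adjusted | n per group for 80% |
|---|---|---|---|---|---|---|
| 0 | 15.00 | 5.14 | 2.92 | 0.81 | 1.00 | 17 |
| 0.05 | 14.62 | 5.01 | 2.99 | 0.83 | 1.03 | 16 |
| 0.10 | 14.23 | 4.88 | 3.07 | 0.85 | 1.05 | 16 |
| 0.20 | 13.42 | 4.60 | 3.26 | 0.88 | 1.12 | 14 |
| 0.30 | 12.55 | 4.30 | 3.48 | 0.92 | 1.20 | 13 |

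**3. Effect of blocking.** A simulation of the linear model at one time point used 51 participants, three arms, two equally likely strata and 3,000 runs per setting. Each cell shows without / with the stratum.

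| Setting | Type I error | Power | Mean interval width (ml) |
|---|---|---|---|
| R² 0.20, blocked | 0.029 / 0.047 | 0.83 / 0.89 | 20.7 / 18.5 |
| R² 0.30, blocked | 0.019 / 0.048 | 0.86 / 0.93 | 20.8 / 17.3 |
| R² 0.20, not blocked | 0.054 / 0.050 | 0.80 / 0.87 | 21.1 / 19.0 |

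The conservative test appears only with blocking. With blocking, the unadjusted power is also a little above 0.81, so the gain at R² = 0.20 is 0.83 to 0.89.

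**4. Which contrast gains.** Take 18 per group (90 less 40% leaves 54) and an assumed intraclass correlation of 0.6, so the within-participant variance is 225 × 0.4 = 90.

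- Group difference at one time: SE = √(2 × 225/18) = 5.00 without the stratum, and √(2 × 180/18) = 4.47 with it at R² = 0.20.
- Group difference in change between two times: a stratum effect that is constant over time cancels, and SE = √(2 × 2 × 90/18) = 4.47 either way.

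Simulating the mixed model agreed: 4.97 against 4.43 for the first contrast, and 4.46 against 4.46 for the second.

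**The case against.** The strongest reply is that no stated claim fails. The 17 per group reproduces without any covariate, any error in the test is in the conservative direction, and no bias follows. The variance share is also unknown. The stratum is a two-level self-report of sputum when well, the outcome is measured during an exacerbation, and the Introduction itself says that sputum volume and consistency differ between those states. A small R² is plausible, and at 0.05 the gain is about two percentage points of power. All of this stands and limits the point to lost efficiency.

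Three stronger readings are tempting, and the protocol does not support them.

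- *No model at all adjusts for the stratum or baseline.* The secondary models list no terms, so nothing is excluded. Covariates may sit in an analysis plan that is not shown. Repeated-measures models are also foreseen where appropriate, so early values can enter as outcomes.
- *The primary analysis ignores early sputum values.* Day 2 is one of the time levels in the mixed model. Whether it is a pre-treatment value is unclear, because day-2 sputum is collected around a supervised session, while Recruitment and randomisation places baseline outcome measures before allocation.
- *The rank-based fallback condemns the secondary analysis to many unadjusted tests.* The Kruskal–Wallis test, which "will be used to compare differences in scores on each instrument between groups at each of the different time points", applies only if regression assumptions fail and is given as an example.

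**Conclusion.** The point holds for the primary model as written. It omits the only stratification factor, and if that factor is prognostic, between-group contrasts in 24-hour sputum at a given time are less precise than they could be. For R² from 0.05 to 0.30, adjusted power at 17 per group is about 0.83 to 0.92 against 0.81, and the unadjusted interval is 3% to 20% wider. At R² = 0 there is no gain. The R² values are assumptions, and the calculation treats a single-time comparison of two groups. The group-by-time interaction gains essentially nothing if the stratum effect is constant over time.

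A reader might infer that the trial is underpowered or that its error rate is wrong. Neither follows. The planned 80% power stands without adjustment, and a type I error below 5% requires blocking within strata, which the protocol does not state. Nor does the argument about wide intervals carry over directly to the logistic and Cox models, where leaving out a prognostic factor mainly pulls the estimate towards no effect.

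This is a free improvement to a valid analysis.

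**What to change.** - Add the randomisation stratum as a fixed effect in the primary mixed model, beside group, time and their interaction.
- Carry the same term into the secondary regression models.
- For continuous secondary outcomes, adjust for the baseline score where one was truly taken before allocation, and state which measurement that is relative to day 2.
- Minor: the strata read as below one or above one "teaspoon sputum per day when well) or high volume", so a participant reporting exactly one teaspoon belongs to neither. Word them as < 1 and ≥ 1 teaspoon.

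The stratum is already known at randomisation, so the model change costs only wording and one degree of freedom. It should be fixed before any outcome data are compared by group.

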#### Ethical considerations

The chief investigator or research assistant will approach potential participants, and provide the information sheet and informed consent form, as well as address any questions or concerns potential participants have. Participants will be informed in writing that their participation in the research study is voluntary, and that if they decide to participate, they can withdraw at any time without providing a reason. Participants will be advised that if they decide not to participate or withdraw from the research study it will not disadvantage them in any way. They will also be advised that their decision to participate or not will not affect their access to medical services or their relationship with any health care professionals involved in their care. Potential participants will have up to one day to consider participation prior to enrolment. The treating clinical staff will not initially approach potential participants about the study, to minimise the risk of coercion. All data will be de-identified through the use of assigned unique codes.

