#### Monitoring

Data monitoring will be performed by the chief investigator throughout the data collection process, with the support of the wider research team, to ensure data quality is maintained.

The researchers will monitor the conduct and progress of the research through regular team meetings for the project duration, and annual reports to the ethics committees. The research assistant and the treating ward physiotherapists in collaboration with the chief investigator will monitor the participants throughout the study and advise the participants’ treating respiratory physicians if a significant deterioration in any outcome measure is detected. Any adverse events will be recorded/documented by the treating physiotherapist or research assistant and reported to the chief investigator, whether the event is related to the research study or not. If any serious adverse events occur that are related to the study during the data collection time, these will be reported promptly to the chief investigator of the study, who will then urgently report the event to the relevant ethics committees. Any reported events will be reviewed in detail by the research team to ensure that the event does not occur again.

The study will end once all data has been collected or upon completion of funding/ethical approval. No interim analyses are planned. There are no provisions available for post-trial care, however education will be provided by a physiotherapist regarding continuing an appropriate airway clearance regimen at their final review as part of the study.

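### The chief investigator fills the allocation envelopes and may also recruit, so allocation concealment is not assured for patients whom the chief investigator approaches

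*Protocol article*

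**What the plan says.** The Allocation section describes a computer-generated sequence for three groups, "with the allocation stratified by participant self-reported usual volume of sputum production" (low or high). The allocations are "placed into numbered sequences (one for each strata) of opaque envelopes by the chief investigator". On the later handling of these envelopes, the section adds a safeguard: "which will only be opened by the treating physiotherapist once baseline measures are completed". It then states: "Only participants and treating physiotherapists will have knowledge of the group allocation".

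Under Recruitment and randomisation, "potential participants will initially be approached by the chief investigator or a research assistant", who explain the study verbally and in writing. If the patient consents, "then baseline outcome measures will be collected prior to group allocation". Ethical considerations confirms the roles: "The chief investigator or research assistant will approach potential participants, and provide the information sheet and informed consent form", and the same two roles answer patients' questions.

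The article does not say who generates the sequence. It does not say how recruitment is divided between the chief investigator and the research assistant, and it does not bar the chief investigator from recruiting.

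**The concern.** Allocation concealment means that whoever decides which patients to approach, when, and how to present the trial cannot know the next assignment. Envelopes achieve this only if the person who prepares them stays out of recruitment. Here one person may do both.

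If a recruiter can foresee the next arm, the choice or timing of approach can depend on it, even unintentionally. The groups may then differ at entry. Assessor blinding, which this trial plans, acts after allocation and gives no protection. The risk is relevant because the primary outcome is sputum weight, and a patient's sputum production can be learned before enrolment. Stratification balances usual volume only across a one-teaspoon-per-day cut, so variation within each stratum remains.

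**Working it through.** No figure in the plan bears on this point, so the check compares the statements on roles.

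**Who does what**

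| Step | Role | Section |
|---|---|---|
| Generate sequence | Computer; operator not stated | Allocation |
| Put allocations into numbered envelopes, one sequence per stratum | Chief investigator | Allocation |
| Approach patients | Chief investigator or research assistant | Recruitment and randomisation |
| Provide information and consent form, answer questions | Chief investigator or research assistant | Ethical considerations |
| Open envelope, after baseline measures | Treating physiotherapist | Allocation |

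The chief investigator appears both in the envelope row and in the two recruitment rows.

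**What a recruiter would need in order to foresee an allocation**

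1. *Access to the order.* Filling numbered envelopes gives this. Opacity and late opening are safeguards against other people. No step is described that masks the contents from the person filling them.
2. *The patient's stratum.* This is self-reported usual sputum volume, which can be learned in conversation.
3. *The current position in that stratum's sequence.* The article neither gives this to the chief investigator nor withholds it.
4. *Room to act on it.* There is some. The article allows a 48-hour window to assess eligibility and up to one day for the patient to decide, and some exclusions call for judgement, such as haemodynamic instability or severe cardiovascular disease. Daily screening and the rule against later reassessment narrow this room but do not close it.

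Item 1 follows from the text, item 2 is easily met, item 3 is open, and item 4 is partly met. Concealment therefore cannot be taken as assured when the chief investigator makes the approach.

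**How many patients**

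Let p be the share approached by the chief investigator. The number exposed is p × 90, where 90 is the number sought under Sample size. The article does not give p. At p = 0 the number is 0, and at p = 1 it is 90.

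For patients approached only by the research assistant, the order consent, baseline, then opening by the physiotherapist can conceal the allocation as intended.

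**The case against.** The strongest reply is that the text shows access, not knowledge. Placing allocations into envelopes does not prove that the chief investigator keeps or remembers a list, and using one would require tracking the position in two stratum sequences across two hospitals. A journal article may also leave custody of the list to the full protocol. This limits what can be claimed. It does not remove the point, because the article itself assigns both tasks to the same role. That is an arrangement stated in the text, not a detail left out.

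Four stronger readings are tempting and are not supported:

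- *Allocation is unconcealed throughout, with every assignment known to a recruiter.* The research assistant may recruit instead, and the envelopes can work for those patients.
- *The sentence on who knows the allocation is false.* It follows the envelope-opening sentence and precedes those on assessor blinding, so it can be read as describing who knows a participant's group after opening. It leaves the chief investigator's access unaddressed, which calls for reconciliation.
- *The chief investigator's data-monitoring role makes concealment worse.* Under Monitoring, that role concerns data quality during collection and has no bearing on concealment at entry.
- *The bias can be put in millilitres.* The documents give neither a share of patients selected nor a difference in sputum between them, so any such figure would only restate what was assumed.

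It may also be said that imbalance can be handled in the analysis. Baseline measures and severity are recorded before allocation, so measured imbalance can be seen and adjusted for. Selection on unmeasured features cannot.

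**Conclusion.** The point holds in a limited form. As written, the plan gives a person who may recruit access to upcoming allocations, and nothing in the article removes that access. Concealment is not assured for the patients whom that person approaches. Their number is unknown, and the effect on the results cannot be quantified from the documents.

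The conclusion rests on two assumptions: that filling the envelopes exposes their contents to the person filling them, and that the chief investigator does approach some patients, as the text permits. If the full protocol rules out either, the article needs only a clarifying sentence. Otherwise the roles should be separated, since the safeguard costs almost nothing and analysis cannot fully restore it afterwards.

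**What to change.** Adopt one of two arrangements and state it in the Allocation section:

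1. An existing team member with no role in screening, consent, treatment or assessment generates the sequence and fills sealed, sequentially numbered opaque envelopes. The chief investigator does not see the sequence.
2. The research assistant alone approaches and consents patients, and the chief investigator takes no part in recruitment.

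Reword the sentence on who knows the allocation so that it separates access to the sequence before enrolment from knowledge of a participant's group after opening.

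If recruitment has begun, apply the chosen arrangement to all remaining allocations. Under the first option, replace the unopened envelopes with ones prepared from a new list. In either case, report the date of the change.

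The cost is a short amendment and, under the first option, a few hours of an existing team member's time. The second option moves the chief investigator's share of recruitment work to the research assistant.
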